## Abstract

**Background:**

Evidence-based treatments for child mental health problems are not consistently available in public mental health settings. Expanding availability requires workforce training. However, research has demonstrated that training alone is not sufficient for changing provider behavior, suggesting that ongoing intervention-specific supervision or consultation is required. Supervision is notably under-investigated, particularly as provided in public mental health. The degree to which supervision in this setting includes ‘gold standard’ supervision elements from efficacy trials (e.g., session review, model fidelity, outcome monitoring, skill-building) is unknown. The current federally-funded investigation leverages the Washington State Trauma-focused Cognitive Behavioral Therapy Initiative to describe usual supervision practices and test the impact of systematic implementation of gold standard supervision strategies on treatment fidelity and clinical outcomes.

**Methods/Design:**

The study has two phases. We will conduct an initial descriptive study (Phase I) of supervision practices within public mental health in Washington State followed by a randomized controlled trial of gold standard supervision strategies (Phase II), with randomization at the clinician level (i.e., supervisors provide both conditions). Study participants will be 35 supervisors and 130 clinicians in community mental health centers. We will enroll one child per clinician in Phase I (N = 130) and three children per clinician in Phase II (N = 390). We use a multi-level mixed within- and between-subjects longitudinal design. Audio recordings of supervision and therapy sessions will be collected and coded throughout both phases. Child outcome data will be collected at the beginning of treatment and at three and six months into treatment.

**Discussion:**

This study will provide insight into how supervisors can optimally support clinicians delivering evidence-based treatments. Phase I will provide descriptive information, currently unavailable in the literature, about commonly used supervision strategies in community mental health. The Phase II randomized controlled trial of gold standard supervision strategies is, to our knowledge, the first experimental study of gold standard supervision strategies in community mental health and will yield needed information about how to leverage supervision to improve clinician fidelity and client outcomes.

**Trial registration:**

ClinicalTrials.gov NCT01800266

## Background

A substantial number of evidence-based treatments (EBTs) for child and adolescent mental health disorders exist, many with multiple randomized controlled trials (RCTs) supporting efficacy in improving outcomes and functioning [1]. EBTs are treatment approaches that have met strict criteria for efficacy based on rigorously controlled studies [2]. However, outcomes for youth served in community-based, public mental health settings have been less positive [3], and direct randomized comparisons of EBTs to usual treatment in such settings have shown variable findings and modest mean effect sizes [4,5]. Initial efforts to bridge the gap by providing access to EBTs through clinician training were mostly insufficient, as they did not include a focus on key implementation factors beyond training, and resulted in little to no change in clinician practice [6]. Therefore, EBT implementation in community-based settings has been viewed as proceeding at ‘an unacceptably slow pace’ [7]. Training in an EBT may be necessary—but not sufficient—to improve client outcomes for the average client served. Two recent reviews of clinician training concluded that training efforts must be active, multi-component, and attend to contextual factors such as organizational support [8,9]. One organizational support factor highlighted as critical, yet receives little research attention, is supervision. According to Herschell [9], the field requires ‘a better understanding of how supervisors should be trained and included in the implementation process.’ Clinical supervision and consultation are potentially the ‘least investigated’ aspects of implementation [10,11] despite findings that supervision accounts for a significant proportion of variance in client outcomes (16%) [12].

### The role of community-based supervisors in supporting EBT delivery

The majority of community-based mental health settings provide some form of ongoing clinical supervision [13], yet the role of community-based supervisors (CBS) in supporting EBT has been largely overlooked [14]. Local supervision, unlike external expert consultation, is generally included within existing organizational and funding structures. Community-based supervision holds promise as a more natural and potentially sustainable mechanism for supporting EBT if used effectively. Very little research—most employing non-experimental designs—has focused on CBS supervision strategies, such as content, techniques (e.g., active listening, role-play, review of case notes) and focus (e.g., past sessions, upcoming sessions), and how CBS can feasibly and effectively support clinicians in providing EBT [15,16]. This has created a critical gap in the implementation literature. What is known suggests that supervision varies considerably and rarely, or inconsistently includes ‘gold standard’ supervision strategies, with limited attention to common EBT techniques like assignment and review of client homework [17,18]. CBS have a variety of competing supervision demands, including overseeing billing, productivity, case management, professional development, and administrative tasks—all important from the organization’s perspective—as well as supervising actual clinical content and interventions. It may be challenging for CBS to allocate sufficient time to the types of supervision activities that are commonly part of supervision in RCTs, and may be necessary to support EBT, such as ongoing skill building through practice and feedback and observation of actual practice [19,20], when balancing all of these responsibilities. Additionally, the dose of supervision may be smaller in community settings than in RCTs. When looking within the broader supervision literature (i.e., beyond CBS), not only are experimental studies missing, but available studies are plagued by a variety of methodological flaws, including small sample sizes, reliance on only self-report, and problematic outcome measures [10].

Because clinicians are the direct service providers, most dissemination and implementation (DI) efforts predominantly or exclusively focus on clinicians, despite high turnover rates. In comparison, supervisors, although providing less direct service, have significant influence on clinicians and may have lower rates of turnover (e.g., [21]). To facilitate DI, Chorpita and Regan [22] suggest that we may need to advance beyond examining practices with real-world clinicians and clients to examining ‘real-world supervisors and managers.’ In particular, ongoing supervision support for providers may be even more important than initial training. In a recent RCT of varying training approaches, the dose of model-specific supervision received, and not the training approach, predicted clinician fidelity to cognitive behavioral therapy (CBT) practice post-training [23].

### ‘Gold standard’ supervision strategies

In efficacy trials and expert consultation models, a relatively common set of ‘gold standard’ supervision strategies have been used to support clinician fidelity and, in turn, positive client outcomes [24-27]. Fidelity is defined as ‘the degree to which an intervention was implemented as it was prescribed in the original protocol as it was intended by the program developers’ [28]. These supervision strategies typically include some combination of four elements: fidelity monitoring, skill building/behavioral rehearsal, review of actual practice (via live observation or tape review), and symptom monitoring. However, there is little empirical guidance around which strategies are most critical, which combinations are most effective, and how these elements can be implemented effectively and efficiently (i.e., feasibly) in community-based settings [29]. According to Garland et al. [30], defining ‘what works’ in implementation research must also include what is ‘practical, feasible, and affordable, and therefore, what is effective.’

Each of these four ‘gold standard’ supervision elements can be challenging to implement in community-based care given resource limitations [31]. This is certainly true of fidelity or treatment integrity monitoring, as priorities of valid, effective measurement must be balanced by priorities for efficient measurement (e.g., feasible, acceptable) [26]. For example, indirect methods such as clinician self-report have relatively poor concordance with objective observer ratings of actual in-session practice (e.g., [32]), but direct methods, including review of actual in session practice, are more expensive and time-consuming [33,34] and ‘differ considerably from most psychotherapy supervision’ [16]. Alternatively, skill building/behavioral rehearsal (BR) may provide a particularly cost-effective proxy for obtaining objective ratings of actual practice in community settings [35], in that the supervisor can observe demonstration of core treatment elements via role-play [36,37]. When combined with other strategies, BR may be a valid, feasible, and effective fidelity monitoring strategy that also allows for ongoing skill building and coaching to fidelity [36,38]. Of note, BR with simulated patients is considered a form of direct observation [33,39] in medical education, but it has received little research attention in mental health.

In contrast to the above clinician-focused gold standard strategies, symptom monitoring (SM) is a different, client-focused gold standard supervision element used in many efficacy trials and is a primary element in measurement-based practice [40]. Ongoing client SM provides a means for regularly assessing client functioning and response to the intervention [41], as it allows the supervisor (and clinician) to monitor client response even in the absence of direct client observation [42,43]. Like the other gold standard strategies, SM has not been fully implemented in most community settings [44,45]. Ideally, supervision integrates data on clinician practice (first three gold standard strategies) with data on client response (SM), to highlight when and to what extent intervention approaches are effective or ineffective.

### Supervision, fidelity, and client outcomes

One of the primary goals of the gold standard supervision strategies is to improve clinician fidelity, as the research literature generally supports a link between model fidelity and client outcomes (e.g., [46,47]; see [48] for an exception) although the strength of the relation varies. Stronger associations between fidelity and outcomes are seen in effectiveness trials, likely due to required high fidelity in efficacy trials creating a floor effect [49]. The literature on the association between supervision and client outcomes is limited but important, as improved client outcomes are the ‘acid test’ for defining good supervision [50]. Available studies suggest that supervision focused on coaching to fidelity predicts better client outcomes [16,51], which may be particularly important when providers are confronted with more heterogeneous or challenging clients [52]. There is also evidence that supervision is related to broader implementation outcomes beyond fidelity. Specifically, EBT coaching in supervision [53] and quality of supervision [54] have been associated with decreased burnout or emotional exhaustion, turnover intention [54], and actual turnover among clinicians [53].

To our knowledge, studies experimentally testing gold standard supervision strategies in community settings have not been conducted, limiting knowledge about how to leverage an important existing mechanism in community mental health to support EBT delivery. Studies are needed that describe usual care supervision, moving beyond self-report, and most importantly, that empirically test the differential impact of implementing gold standard supervision strategies in usual care. To maximize the impact of implementation efforts in the area of supervision, the field needs practical recommendations taking efficacy, efficiency, and feasibility into account to address questions such as: What are the current supervision strategies most commonly utilized by CBS trained in EBT? What techniques do they use, what content (e.g., EBT components, case management) is discussed, and temporally, on what do they predominantly focus (past sessions; upcoming sessions)? Which gold standard supervision strategies, if incorporated into CBS supervision, predict better clinician fidelity and client outcomes?

## Methods/Design

We propose a two-phase, mixed within- and between-subjects design studying supervision of an EBT for child trauma exposure sequelae, Trauma-focused Cognitive Behavioral Therapy (TF-CBT) [55] (see [1] for a review). In Phase I: Baseline and Descriptive Study, we will examine current ‘usual care’ supervision strategies (i.e., supervision baseline) of CBS who are trained in and supervise TF-CBT—including content, techniques, and focus, particularly the use of any gold standard techniques. Phase I will also yield some information on supervision dose (e.g., duration per clinician, per case; weekly consistency or inconsistency). In Phase II: Randomized Trial, clinicians will be randomized to one of two supervision conditions, both of which systematically include gold standard strategies: Symptom and Fidelity Monitoring (SFM) or SFM plus Behavioral Rehearsal (SFM + BR). In SFM, the focus is on systematic monitoring of client symptoms and fidelity, but only via clinician self-report given the challenges of direct methods (e.g., observation of actual practice) in community-based settings. In SFM + BR, the addition of BR provides a strategy that is potentially both a feasible proxy for direct methods and an opportunity for skill building. Primary aims across both phases are to describe current supervision practices and to examine the impact of including gold standard elements on clinician fidelity and client outcomes.

Our design leverages and builds on the existing funding and efforts provided through the Washington State Trauma-focused Cognitive Behavioral Therapy Initiative (WA TF-CBT Initiative). The structure for the WA TF-CBT Initiative is similar to the other 17 statewide initiatives (see [56-58]) and to national and statewide DI efforts of other EBT (e.g., NY’s Achieving the Promise for Children, Youth, and Families [59]). Since 2007, the initiative has trained clinicians and supervisors from across the state in TF-CBT. It provides some supervisor-specific training (one-day training yearly) and support (i.e., monthly consultation call, listserv) for CBS. The proposed study builds on this initiative, offering a unique opportunity to study supervision of an EBT in community-based settings. Participation in the state-funded WA TF-CBT Initiative has been geographically diverse, with involvement from over 60 public mental health agencies and nearly 900 clinicians and CBS statewide. These agencies are from urban and rural areas, some of which serve predominantly ethnically diverse populations.

### Clinician and supervisor participants

Participants will include 35 supervisors and 130 clinicians from an estimated 15 to 20 agencies. Agencies were selected from those in the WA TF-CBT Initiative with consideration of statewide geographic representation. Each agency has one to four supervisors and a potential clinician participant pool of 2 to 15 qualifying clinicians based on study inclusion and exclusion criteria. Eligible supervisors were identified during study development with additional supervisors recruited at the beginning of Phase I. Eligible clinicians must be: trained in TF-CBT as part of the WA TF-CBT Initiative and/or have completed the TF-CBT web training with at least one TF-CBT case underway; at least 50% FTE employees at one of the participating agencies; supervised by one of the participating supervisors; and able to provide TF-CBT in English. We propose only two exclusionary criteria: immediate plans to leave the agency or transition into a non-child/adolescent caseload carrying position. Clinicians and supervisors who exit the study will be replaced with new clinicians and/or supervisors who are similarly trained in TF-CBT and study protocols.

### Children and adolescents

We will recruit one child/family per clinician in Phase I, and three children/families per clinician in Phase II. Eligible children and adolescents will be clients at one of the participating agencies. Inclusion criteria include: age 6–17; trauma history; significant posttraumatic stress (PTS) symptoms; live with a parent/legal guardian who is willing to participate in the study; the child is English-speaking; and treatment approach will be TF-CBT. Exclusionary criteria are intentionally limited and include only: presence of a pervasive developmental disorder or cognitive impairment and parental serious mental illness. Clinicians are asked to introduce the study to caregivers of all potentially eligible youth who meet these inclusion and exclusion criteria. If interested, study staff proceed with recruitment.

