### Phase II study

In Phase II of the study, all clinicians will be randomized to one of two supervision conditions: Symptom and Fidelity Monitoring (SFM) or SFM plus Behavioral Rehearsal (SFM + BR). We will randomize by clinicians because they are our primary unit of analysis. Supervisors will provide both conditions to balance the impact of individual supervisor/agency factors across conditions. We will monitor supervisor adherence to condition protocol and experimental drift through coding of audiotapes of supervision sessions. During Phase II, four randomly selected meetings per supervisor (two for each condition, distributed across participating clinicians) will be reviewed within a two-week window of the supervision meeting occurring (which is possible due to near real-time uploading with the use of the mobile device system) by research assistants blind to study condition. If experimental drift is identified, supervisors will be contacted within two weeks for a booster training on the supervision conditions. Supervisors will receive a biweekly email on condition adherence so that all supervisors receive regular communication from our team related to provision of supervision conditions.

Phase II has the added benefit of a within-subject design, in which clinicians retained from Phase I serve as their own controls prior to randomization. Given clinician attrition and replacement, some clinicians will not have Phase I data, and therefore will only be part of the between-subject analyses. Fidelity scores will be obtained from the three Phase II enrolled clients per clinician to obtain precise and reliable estimates of effect (see earlier ‘Objective TF-CBT fidelity’ section) and to increase statistical power for detecting differences between the two intervention conditions.

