### Symptom and fidelity monitoring plus behavioral rehearsal (SFM + BR)

The SFM + BR condition includes the SFM components and an additional, multipurpose strategy—behavioral rehearsal (BR). Given concerns about relying on clinician self-report of fidelity (i.e., indirect methods) and the importance of skill building, the inclusion of BR is a potentially high-yield addition [27]. In SFM + BR, supervisors will conduct a TF-CBT component BR (e.g., five to ten minutes) relevant to an upcoming session in each supervision meeting and provide feedback. Supervisors will have a short set of guidelines (e.g., bulleted form) that detail expected content and techniques for BR of each TF-CBT component. Guidelines focus specifically on common challenges for TF-CBT components (e.g., dealing with avoidance, homework assignment/review).

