### Limitations

The proposed study is one of the first to experimentally examine supervision strategies in community mental health, though it is not without its limitations. First, to obtain similar samples of supervision, some frequently used types of supervision could not be included (i.e., group supervision, ‘drop by’ or informal supervision). Informal supervision, in particular, is likely to be quite frequent, particularly for certain agencies and supervisory relationships. Second, as fidelity is one of our primary outcomes, permission to receive audio recorded TF-CBT sessions is needed, precluding examination of fidelity with the clinician’s full caseload. Third, clinicians invite clients to participate, and despite requests that clinicians invite all who meet eligibility and exclusionary criteria, we cannot be sure that enrolled cases are representative of their caseload. Fourth, conclusions drawn from analyses comparing Phase I and Phase II outcomes may be limited, as child cases could not be randomly assigned to ‘usual care’ supervision or one of the Phase II RCT conditions, given the temporal ordering of the study phases. Fifth, although TF-CBT is similar to other CBT-based approaches, the focus on a specific treatment (i.e., TF-CBT) and treatment population (trauma-exposed) allows for careful examination of the implementation of the protocol’s treatment components with fidelity, but may limit generalizability of findings to supervision of other treatments and populations of focus. Finally, another potential limitation is selection effects; the supervisors who agreed to participate may not be representative of public mental health supervisors in general in that all have received EBT training are positive about TF-CBT as an intervention and the enterprise of implementing EBT in public mental health.

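### Phase II children are enrolled after clinicians are randomised, through clinicians who cannot be masked, so the enrolled children can differ between SFM and SFM + BR

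*Protocol article*

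**What the plan says.** The protocol article, under Children and adolescents, plans "three children/families per clinician in Phase II". The route into the study runs through the treating clinician: "Clinicians are asked to introduce the study to caregivers of all potentially eligible youth who meet these inclusion and exclusion criteria". Study staff act only after that step: "If interested, study staff proceed with recruitment". One inclusion criterion, "treatment approach will be TF-CBT", is itself a treatment decision.

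Under Phase II study, "all clinicians will be randomized to one of two supervision conditions". Phase I comes before that step, since "clinicians retained from Phase I serve as their own controls prior to randomization". The section on the SFM + BR condition says that "supervisors will conduct a TF-CBT component BR (e.g., five to ten minutes) relevant to an upcoming session in each supervision meeting and provide feedback"; SFM has no such component. The only masking that the article mentions is for the research assistants who review supervision recordings for adherence.

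The Limitations section recognises that clinicians issue the invitations and that, whatever they are asked to do, "we cannot be sure that enrolled cases are representative of their caseload". Its separate caveat about children not being randomly assigned concerns Phase I against Phase II.

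**The concern.** Randomising clinicians balances clinicians. It balances children only if the way children enter the study is unrelated to the arm. Here they enter after allocation, through a person who knows the allocation. If clinicians in the two arms differ, even unintentionally, in which families they raise the study with or which cases they plan to treat with TF-CBT, the groups compared in Aim 2 differ for a reason other than supervision.

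The Limitations section describes the mechanism but draws only the external consequence, that enrolled cases may not reflect the caseload. The internal consequence is that selection could differ between SFM and SFM + BR and so bias the randomised contrast. A difference between the arms, or the absence of one, could then partly reflect who was enrolled. Coded fidelity is exposed because it can plausibly depend on how workable a family is, and client outcome because families can differ in expected response. The Aim 3 mediation analysis would inherit both.

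**Working it through.** **1. Order of events.** Phase I precedes randomisation (Phase II study). The children compared between arms are the three per clinician recruited in Phase II (Children and adolescents). The abstract's total reproduces: 130 clinicians × 3 children = 390. All 390 therefore belong to the phase in which clinicians are randomised.

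**2. Masking.** Rehearsal takes place at every supervision meeting in one arm and is not part of the other, so a clinician cannot be unaware of the condition. The article does not say outright that clinicians know their arm before they introduce each family. That is an inference from steps 1 and 2.

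**3. Gatekeeping.** The clinician introduces the study and plans the treatment approach. Staff see only families who have already been introduced and are interested.

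**4. Exposure of the two Aim 2 models.** The fidelity model is described with supervision as predictor and no named child covariates. The client model is longitudinal with three levels, and scores are collected from the start of treatment. There, a difference in starting severity falls mainly in the intercept. The arm-by-time contrast is biased by selection on expected rate of change.

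**5. Illustration of size.** The documents give no figure for selection bias, so b below is an assumption. Further assumptions are 1:1 allocation, an outcome SD of 1, a two-sided 5% test and one time point. The ICCs 0.04 and 0.24 are taken from the Aim 2 power statements.

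SE = √(4 × (1 + 2 × ICC) / 390)

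- ICC 0.04: √(4 × 1.08 / 390) = 0.105
- ICC 0.24: √(4 × 1.48 / 390) = 0.123

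Error rate when the true effect is zero = 1 − Φ(1.96 − b/SE) + Φ(−1.96 − b/SE)

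| Assumed b (SD) | b as share of the 0.35 effect | Error, ICC 0.04 | Error, ICC 0.24 |
|---|---|---|---|
| 0 | 0% | 5.0% | 5.0% |
| 0.05 | 14% | 7.6% | 6.9% |
| 0.10 | 29% | 15.8% | 12.8% |
| 0.20 | 57% | 47.6% | 36.8% |

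The 0.35 is the small effect named in the fidelity power statement. More children would not reduce b; a smaller SE would make the same b more damaging.

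**The case against.** The strongest reply is that the plan already states the right rule, that clinicians should introduce the study to every potentially eligible family, and that an article would not normally list screening logs or covariates. Much of this stands, and several stronger readings should be resisted.

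- *That nothing checks the invitation rule.* A reader might infer this, but the full protocol is not shown and may contain such a check. What the article itself shows is that its authors do not regard compliance as assured and do not draw the between-arm consequence.
- *That clinicians have wide freedom to pick three families.* No count of eligible TF-CBT clients per clinician is given. Clinicians may work half time, the web-training route needs only one TF-CBT case under way, and child eligibility has several conditions. For some clinicians, three families may exhaust the supply.
- *That SFM + BR clinicians would favour easier families because they are observed on each case.* The condition requires one short role-play per supervision meeting, not observation of each case. Recording, symptom measures and fidelity checklists apply in both arms. The incentive to select differently may be weak, and no direction is established.
- *That a baseline severity difference passes straight into the client result.* In the longitudinal model it falls mainly in the intercept.
- *That the error rates above are estimates.* They follow from assumed biases in a simpler model than the one planned.

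Supervisors also deliver both conditions, which balances supervisor and agency factors. It does not balance the children enrolled under each clinician. The structural point therefore survives: entry after allocation, through an unmasked gatekeeper, with the consequence for the randomised contrast not recognised.

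**Conclusion.** The point holds as a statement of possibility: enrolled children can differ between SFM and SFM + BR. The article does not show that they will differ, in which direction or by how much. The conclusion rests on the inference that clinicians know their condition when they introduce families, which follows from the order of events and from an intervention that cannot be masked.

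On the assumed values, a selection difference of 0.05 SD does little harm, with an error rate of about 7-8%. A difference of 0.10 SD is material, at about 13-16%. These figures indicate sensitivity only. For client outcomes they apply to a simple comparison of means, not to the change-over-time contrast.

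This is worth correcting because the remedy is cheap and acts on the trial's main comparison. It does not invalidate the design.

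**What to change.** 1. **Children and adolescents, for Phase II.** Have each clinician invite eligible families consecutively by TF-CBT start date until three consent. Keep a brief tablet log of each eligible, invited and consented case. Report these proportions, and child baseline values, by arm.
2. **Aim 2, fidelity model.** Adjust for child age, baseline PTSD-RI and baseline parent SDQ. All are available: the parent SDQ is completed for every child and the PTSD-RI is given at the start of treatment.
3. **Aim 2, client model.** Keep the start-of-treatment score as an outcome and base the arm contrast on change over time. Adjust for child age and the baseline of the other measure (PTSD-RI when SDQ is analysed, and the reverse), allowing these to act on change as well as on level. Do not also enter the same baseline score as a covariate, since it would then stand on both sides of the model.
4. **Limitations.** Extend the sentence on representativeness to say that selection may differ between the randomised arms.

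The cost is a little clinician time and less freedom over which family to invite. No extra children, staff or measures are needed. At submission Phase II had not begun, so the change could precede its recruitment. The log and adjustment reduce and expose selection but do not remove it, because the clinician still decides whether a child's treatment will be TF-CBT and would also keep the log.
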